#### Randomization

Before randomization, a blinded researcher will conduct the neuropsychological battery and the participant will complete the baseline fMRI. There will be one unblinded independent researcher who will conduct the randomization sequences in order to keep study researchers blinded to group. The randomization sequences are balanced in blocks of random size (2, 4) to prevent researchers from guessing what the next participant’s condition assignment might be. After the neuropsychological testing and fMRI have been completed, the unblinded researcher will assign a study ID to the participant, using a pre-populated form from the statistician’s randomization assignment, which will determine the study condition the participant will receive: PS/EF CCT, verbal CCT, or waitlist control. The Peak account information will be generated after the neuropsychological battery and fMRI have been completed. The unblinded researcher will then assist the participant in downloading the Peak application to their mobile phone or tablet. Participants will receive a specific Peak account and email using only their study IDs to ensure that their data is de-identified.

#### CCT modules

No training sessions are provided to the participants; participants are told to contact the research team if they have any questions regarding how to use the application or play the games, or if they have difficulty accessing the application. Peak does not provide technical support directly to the participants. Participants randomized to the PS/EF CCT group will play the following five modules: Must Sort, Face Switch, Refocus, Tunnel Trance, and True Color (descriptions of these games are found in Table 2). Participants will be able to choose which modules to play during each training session. The selected games will tap into processing speed and executive function skills by necessitating quick responses. Repeated practice of these skills over time that scales in difficulty in response to the participant’s performance drives improvement of these abilities. The selected games reflect the deficits characteristic of depression in young adults. The active control condition (verbal CCT) is identical to the PS/EF CCT condition in duration, training platform, and frequency of sessions. Participants in this condition will complete the following five modules that tap into verbal ability: Word-A-Like, Word Pairs, Worth Path, Word Fresh, and Babble Bots (descriptions of these games are found in Table 3). Participants will be able to choose which modules to play during each training session. Participants randomized to waitlist control will undergo all assessment and imaging procedures but will not receive CCT until after 8 weeks. Participants in the PS/EF CCT group and the verbal CCT group will spend the same amount of time on the platform during the training phase, which will consist of five 15-minute training sessions per week for 8 weeks (40 total training sessions). Participants will receive automatic feedback within the application about their scores and performance change over time after playing the games. Participants will have access to the games through cellular data or internet connection.

#### Clinic-based clinical, cognitive, and functional assessments

At the screening evaluation, trained research assistants will administer the depression section of the Anxiety Disorders Interview Schedule for DSM-IV (ADIS-IV), 21-item HDRS, and 21-item BDI-II to document depression severity and diagnosis. Participants will also complete the Sheehan Disability Scale (SDS) to determine daily functioning, and the WTAR used in conjunction with demographic variables to estimate IQ. At baseline (week 0), participants will complete a comprehensive clinical and neuropsychological assessment. Clinical and functional assessments administered in person include the HDRS, BDI-II, and SDS. The neuropsychological battery includes the following: Delis-Kaplan Executive Function System (DKEFS) Trail Making Test to assess PS and EF, specifically speeded attention and cognitive flexibility; DKEFS Color-Word Interference Test to assess PS and EF, specifically response inhibition and cognitive flexibility; Wechsler Adult Intelligence Scale, Fourth Edition (WAIS-IV) Digit Span Forwards, to assess immediate attention, and Digit Span Backwards, to assess working memory; WAIS-IV Coding and Symbol Search to assess PS; DKEFS Letter and Category Naming Test to assess verbal fluency; California Verbal Learning Test, Version 2 (CVLT-II) to assess verbal memory; and Brief Visuospatial Memory Test-Revised (BVMT-R) to assess visual memory. Additionally, participants will complete an expectancy scale at baseline which assesses how much they expect to improve during the intervention. Expectancy effects are important to assess given their potential impact on clinical trials research [89,90]. Participants will complete the User Engagement Scale to measure multiple aspects of engagement, usability, and satisfaction.

### Timeline of Longitudinal Assessments

At subsequent clinic visits (weeks 4 and 8 and 3-months), the same neuropsychological and clinical battery will be completed. Participants will complete the User Engagement Scale at week 8. The three-month follow-up visit will be to determine treatment gains and lasting effects of CCT on mood, cognition, and daily functioning.

### Study Measures

Study measures with time-points of administration are listed in Table 4 At screening, the ADIS-IV, HDRS, BDI-II, SDS, and WTAR will be administered, and current medications will be documented. The HDRS, BDI-II, and SDS will be administered again at weeks 0, 4, and 8, and 3-month follow-up. At weeks 0, 4, and 8, and 3-month follow-up, the neuropsychological battery will be administered, and current medications will be documented. At weeks 0 and 8, participants will undergo an MRI scan of the brain. The MRI scan will include the following sequences: T1 Magnetization-Prepared Rapid Gradient-Echo (MP-RAGE), as well as a task-based fMRI sequence consisting of the emotional go/no-go task, and pre-post task-based resting-state fMRI scans (see Table 5).

### Blinded Training Procedure

The blinded research assistant will administer the neuropsychological and clinical battery. The blinded research assistant will be blind to the group assignment of participants, but not to the aim of the research study. The unblinded research coordinator will be responsible for administering the initial Peak instructions and technical support. The unblinded research coordinator will be aware of group assignment and the aim of the research study. Twice per week, the unblinded research coordinator will review the compliance of all participants through the Peak application. The Peak application provides information about how many games each participant plays, which is then used to determine the amount of time the participant spent playing games. Noncompliant participants will be encouraged to participate unless otherwise notified. If there is a period of time where a participant does not train for three days in a row, the unblinded research assistant will call the participant to evaluate why training has not occurred and provide technical support if necessary, in order to ensure high compliance rates.

### Criteria for Early Discontinuation

Early discontinuation may occur due to one or more of the following reasons: (1) the participant’s decision not to continue the computerized training due to lack of time, interest, or motivation; (2) unavoidable circumstances (e.g., moving residence and unwilling or unable to return for in-person evaluations); (3) investigator decision to terminate; (4) death or prolonged hospitalization for medical reasons. We will not terminate participation for non-adherence. If non-adherence occurs, we will document the level of the participant’s adherence and still include the data in intent-to-treat analyses.

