### Treatment Regimen

An initial pre-screening will be completed over the phone to assess initial eligibility criteria. Participants will provide information regarding age, access to smartphone/tablet, MRI contraindications, current/prior engagement in brain training games, and a brief medical history. If deemed eligible, participants will be invited for an in-person eligibility screen, which will assess for depressive symptoms and risk. Participants will be enrolled into the study after screening for eligibility and providing in-person informed consent. The randomization will be assigned by the statistician and then carried out by the unblinded research coordinator. Enrolled participants will engage in four clinic visits (weeks 0, 4, and 8, and 3-month follow-up) and receive two fMRIs (weeks 0 and 8). Participants will also complete an online version of the BDI-II during weeks 2 and 6. To protect study participants, if a participant shows a 20% increase from their baseline BDI-II score for two consecutive timepoints they will be discontinued from the study and provided with referrals for mental health services. This cut-off was made as a clinical decision based on data from our preliminary study [60] as well as research that shows that the minimal clinically important difference for improvement on the BDI-II is a 17.5% reduction in scores [86]. If a 17.5% reduction in BDI-II scores corresponds to a clinically important improvement, it is likely that a similar increase in scores would be a clinically important exacerbation. In our preliminary study [60], the mean baseline score on the BDI-II was 22.98 (SD = 11.58), so a 20% increase would be analogous to a shift from a score of 23 to a score of 28 for two consecutive timepoints. Additionally, BDI-II scores in general, as well as specific items, will be closely monitored. In particular, item 9 of the BDI-II, which assesses for suicidality, will be monitored for every BDI-II for each participant. If a participant at any time indicates an answer ≥ 1 on this item, we will have the participant complete a risk assessment using the Suicide Assessment Five-Step Evaluation and Triage (SAFE-T [87]) with Columbia Suicide Severity Rating Scale (C-SSRS [88]) Protocol, which describes the level of risk and subsequent response required by the research team.

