### Statistical Analysis and Sample Size

Prior to conducting any tests of hypotheses, all data will be reviewed for extreme values using boxplots, scatterplots, histograms, and normal probability plots. When distributional assumptions are not met, data will be transformed or nonparametric procedures will be used. Descriptive statistics will be used to characterize the sample with regard to demographic and clinical characteristics including but not limited to age, education, race/ethnicity, gender, and depression severity.

In this study, missing data patterns will be analyzed explicitly. Data will not be assumed to be missing completely at random (MCAR) or missing at random (MAR). Rather, this assumption will be explicitly tested predicting “missingness” (missing = 1 and not missing = 0) at all assessment points post-baseline with baseline predictors (e.g., clinical, demographic, neuropsychological, and MRI), which can be accomplished in a logistic regression framework. More advanced approaches to handling missing data such as multiple imputation [91] or maximum likelihood estimation will be used rather than older, more biased approaches such as mean substitution, listwise or casewise deletion, or linear regression [92].

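### The early-discontinuation rule does not separate stopping the training from leaving the study, and up to week 8 any data lost this way can come only from the two CCT arms

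*Protocol article*

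**What the plan says.** In the protocol article, Criteria for Early Discontinuation gives four reasons. The first is "the participant’s decision not to continue the computerized training due to lack of time, interest, or motivation". The others are unavoidable circumstances such as relocation that prevents attendance, the investigator's decision, and death or long hospitalization. The paragraph then adds "We will not terminate participation for non-adherence", and for non-adherence promises that "we will document the level of the participant’s adherence and still include the data in intent-to-treat analyses".

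Four other sections bear on this:

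- Treatment Regimen, on worsening BDI-II scores, uses the same word for study exit: "they will be discontinued from the study and provided with referrals for mental health services".
- Blinded Training Procedure provides that after three consecutive days without training, "the unblinded research assistant will call the participant to evaluate why training has not occurred".
- CCT modules says of the waitlist arm that its participants "will undergo all assessment and imaging procedures but will not receive CCT until after 8 weeks".
- Statistical Analysis and Sample Size says that multiple imputation or "maximum likelihood estimation will be used rather than older, more biased approaches such as mean substitution, listwise or casewise deletion".

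**The concern.** Two participants may behave identically in that neither plays the games. One tells the coordinator that they have stopped, and the other simply never opens the app. The first matches a listed reason for early discontinuation. The second is non-adherent, stays in the study and is promised a place in the intent-to-treat analyses. The article does not say that the first is still assessed at week 4, week 8 (with MRI) and 3 months.

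The three-day telephone call makes the boundary unstable, because asking why someone is not training can turn silent non-adherence into a stated decision.

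If the stated decision ends participation, the loss is tied to allocation during the acute trial, since only the CCT arms have training to give up. Hypothesis 1 under both aims compares CCT with waitlist. Interest and motivation are also close to the condition being treated, so those who stop may well differ in outcome from those who continue.

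**Working it through.** **Step 1. Which reading does the text support?**

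| Evidence | Points to |
|---|---|
| The other three reasons (cannot attend, investigator termination, death or hospitalization) end or interrupt participation | Study exit |
| The non-adherence sentence follows as an exception about terminating participation | The list gives reasons why participation ends |
| Treatment Regimen uses the same term for leaving the study | Study exit |
| The first reason names only the training, not the visits | Training stop only |
| No sentence says that assessments cease or data are dropped | Open |

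Study exit is the natural reading but is not stated. What can be established is that two rules cover one behaviour.

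**Step 2. Which arms, and when?** Weeks 0 to 8 contain the week 4 and week 8 visits and both MRI scans. Waitlist participants have no CCT in that period, so the first reason cannot apply to them. They receive CCT afterwards and could stop it before the 3-month visit. The one-sided exposure therefore holds through week 8 and not beyond.

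**Step 3. What can the planned analysis recover?** Maximum likelihood or multiple imputation uses whatever was collected before exit. For HDRS, SDS and TMT-4, a participant who leaves after week 4 still contributes baseline and week 4. For MRI there are scans at weeks 0 and 8 only. The regressed-change model under Aim 2 takes the week 8 connectivity score as its outcome, so a participant without that scan has a baseline covariate, no outcome and no intermediate scan. The planned missingness check uses baseline predictors and can miss loss of motivation that arises during training.

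**Step 4. The plan's own sample-size figure.** The Power section gives 195 in total, or 65 per group, for power 0.8, two-tailed α = 0.05, a medium effect and 20% attrition. Taking medium as f = 0.25 (an assumption), a three-group one-way ANOVA needs 52.4 per group. Then 52 / (1 − 0.20) = 65 per group, and 3 × 65 = 195, so the figure reproduces. The planned total is 90, which is 30 per arm if allocation is equal (also an assumption).

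**Step 5. Illustrative shift in the mean.** Let q be the share of a CCT arm that stops and is not measured, and g the SD by which stoppers' outcomes would have been worse than continuers'. The full-arm mean is (1 − q)·m + q·(m − g) = m − q·g, where m is the continuers' mean. The observed mean is m, so the shift is q·g before any recovery by the model.

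- q = 0.10 (3 of 30), g = 0.3: 0.03 SD
- q = 0.20 (6 of 30), g = 0.5: 0.10 SD
- q = 0.20, g = 0.8: 0.16 SD

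For PS/EF versus verbal, both arms are exposed and only the difference in q·g matters. With equal q and g it cancels. With q of 0.20 and 0.10 and g = 0.5 in both, it is 0.10 − 0.05 = 0.05 SD.

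The document gives neither q nor g. Its 20% attrition figure covers all causes, so 10-20% for this reason alone is a range and not an estimate.

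**Step 6. Illustrative power.** Assumptions: pairwise d = 0.5 (the article gives no numerical effect), two-sided t-test, 30 per arm, and loss for this reason only.

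| Loss in CCT arms | CCT arm vs waitlist | PS/EF vs verbal |
|---|---|---|
| 0% | 0.48 (30 vs 30) | 0.48 (30 vs 30) |
| 10% | 0.46 (27 vs 30) | 0.44 (27 vs 27) |
| 20% | 0.43 (24 vs 30) | 0.40 (24 vs 24) |

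**The case against.** The strongest reply is that the paragraph can be read as harmless. It says only that early discontinuation may occur for these reasons. It does not cancel any visit, and where the authors mean study exit by rule, in Treatment Regimen, they say so outright. Someone who stops the games but still attends is non-adherent in the ordinary sense, and nothing confines the non-adherence sentence to people who keep quiet about it. The compliance section also encourages non-compliant participants until told otherwise, which may already cover a declared stop. A full protocol, not shown, may settle the matter.

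Much of this stands. A reader might infer that the plan discards the data of anyone who announces a stop. The documents do not say so, and data collected before exit would still be used. But the article does more than omit a detail. It states a rule that lists a training stop as discontinuation, next to another that says non-adherence does not end participation. Which rule a site follows decides whether the visit takes place, and no analysis plan can restore a visit or scan that was never held.

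A reader might also infer that only the CCT arms can ever lose data, or that the loss must flatter CCT. Neither is supported. The other three reasons and the BDI-II rule apply in every arm, and waitlist participants may stop CCT after week 8. Loss of worsening waitlist participants under the BDI-II rule would push the other way, and people who stop for lack of time need not be those doing badly.

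**Conclusion.** The point holds as an unresolved conflict between two rules in one paragraph, with a consequence for which data are collected. On the natural reading, participants who declare a training stop leave the study, and through week 8 losses under this reason fall only on the two CCT arms. The repeated clinical outcomes are partly protected by the planned missing-data methods, and the two-scan MRI outcomes hardly at all.

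The size and direction of any bias are not known from the document. The 0.03-0.16 SD range assumes that 10-20% stop and that their outcomes are 0.3-0.8 SD worse, with no recovery by the model. It shows what could be at stake and does not estimate this trial's bias. The power loss is modest: at d = 0.5, from 0.48 to no lower than 0.40 at 20% loss. The article already accepts 90 participants against a calculated 195, however, so avoidable loss is unwelcome. This is worth correcting because correction is cheap, but it does not threaten the trial's validity by itself.

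**What to change.** Reconcile the two rules for data collection and analysis. State that a participant who stops training is handled, for assessment and analysis, as non-adherent:

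- the date and reason are recorded;
- the week 4, week 8 (including MRI) and 3-month assessments already scheduled are still offered, unless the participant withdraws consent to assessment;
- the data stay in the intent-to-treat analysis.

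Record stopping the training and leaving the study as separate events on the discontinuation form. Nothing here asks anyone to continue training, and clinical or safety-based stopping rules, including the BDI-II rule, are left unchanged.

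The cost is one paragraph and one line on a form. The visits are already scheduled for every randomized participant. The downside is some effort to retain people who have lost interest in the games. The change helps only for visits not yet past, so it should be made while participants are still in follow-up.

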### Data Management

Data entry will be completed by graduate and undergraduate research assistants on the study protocol. Data entry will be done throughout the project. Data will be kept in a de-identified file kept on an encrypted password-protected external hard-drive that only research personnel have access to.

### Hypotheses

The primary aim of the study is to determine whether PS/EF-focused CCT is superior to, and leads to faster improvement than, verbal ability-focused CCT and waitlist control. Hypothesis 1: there will be greater improvement in mood, cognition, and everyday functioning in participants randomized to CCT (both PS/EF and verbal) compared to waitlist control. Hypothesis 2: there will be greater improvement in EF and PS outcomes in participants randomized to PS/EF CCT compared to verbal CCT and waitlist control. Hypothesis 3: there will be faster improvement in mood, cognition, and everyday functioning in participants randomized to PS/EF CCT compared to verbal CCT and waitlist control.

The secondary aim of the study is to determine whether PS/EF-focused CCT leads to greater change in CCN activation (task-based fMRI) and connectivity (resting state fMRI) than verbal ability-focused CCT and waitlist control. Hypothesis 1: there will be a greater increase in CCN activation and connectivity among participants randomized to PS/EF CCT and verbal CCT compared to waitlist control. Hypothesis 2: there will be a greater increase in CCN activation and connectivity among participants randomized to PS/EF CCT compared to verbal CCT. Hypothesis 3: clinical improvements will be positively associated with an increase in CCN activity and connectivity.

### Statistical Analysis and Sample Size

Prior to conducting any tests of hypotheses, all data will be reviewed for extreme values using boxplots, scatterplots, histograms, and normal probability plots. When distributional assumptions are not met, data will be transformed or nonparametric procedures will be used. Descriptive statistics will be used to characterize the sample with regard to demographic and clinical characteristics including but not limited to age, education, race/ethnicity, gender, and depression severity.

In this study, missing data patterns will be analyzed explicitly. Data will not be assumed to be missing completely at random (MCAR) or missing at random (MAR). Rather, this assumption will be explicitly tested predicting “missingness” (missing = 1 and not missing = 0) at all assessment points post-baseline with baseline predictors (e.g., clinical, demographic, neuropsychological, and MRI), which can be accomplished in a logistic regression framework. More advanced approaches to handling missing data such as multiple imputation [91] or maximum likelihood estimation will be used rather than older, more biased approaches such as mean substitution, listwise or casewise deletion, or linear regression [92].

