#### Aim 1.

To test for differences in improvement between the three groups on the primary outcomes for mood (HDRS), everyday function (SDS), and executive function (TMT-4), we will use multilevel modeling [93–95]. Multilevel modeling is a powerful and flexible statistical procedure that estimates intercepts and slopes for each individual (level 1) as well as intercepts and slopes for the average individual (level 2) over time using Maximum Likelihood (ML) estimation [93–96]. All analyses will adjust for gender and race/ethnicity (centered at their respective means). Time will also be centered so that the intercept reflects scores at week 4 (middle of the trial). To test whether average scores at week 4 and rate of change differs among the groups (PS/EF CCT, verbal CCT, and waitlist control), dummy variable coding will be used with 1 indicating membership and 0 indicating non-membership. With each covariate centered at its mean, the intercept will correspond to the mean of the reference group at week 4 (waitlist control) and the slope will reflect the difference between the groups included in the model (PS/EF CCT, verbal CCT) and the reference group (dummy coded variable excluded from the model). Because time can be centered at any point in the trial, we will also be able to run models with time centered at weeks 0 and 8 so that the intercept reflects scores at these points in the trial. This will allow us to test the hypothesis that PS/EF-focused CCT is more efficient, and therefore leads to faster improvement, than verbal-focused CCT or waitlist control. The −2LL (−2 Log Likelihood) test will be used to test model fit [94,95].

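### The missing-data text says MAR is tested rather than assumed, but a baseline-only logistic model cannot test MAR, the named methods rely on it, and the described primary models omit the BDI-II scores that trigger withdrawal

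*Protocol article*

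**What the plan says.** Under Statistical Analysis and Sample Size the protocol article says: "Data will not be assumed to be missing completely at random (MCAR) or missing at random (MAR". It then promises an explicit test of the assumption, a logistic regression of a missingness indicator "at all assessment points post-baseline with baseline predictors (e.g., clinical, demographic, neuropsychological, and MRI". The paragraph goes on: "More advanced approaches to handling missing data such as multiple imputation [91] or maximum likelihood estimation will be used", in preference to deletion or mean substitution. No analysis is made conditional on the result of the test.

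Under Aim 1 the "primary outcomes for mood (HDRS), everyday function (SDS), and executive function (TMT-4" are analysed by multilevel models fitted "over time using Maximum Likelihood (ML) estimation". Gender and race/ethnicity are the only adjustment covariates named. BDI-II is a secondary measure and does not appear in these models.

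Under Treatment Regimen, a participant whose BDI-II is 20% above baseline "for two consecutive timepoints they will be discontinued from the study". BDI-II is collected online at weeks 2 and 6 as well as at the clinic visits (weeks 0, 4 and 8, and 3 months).

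**The concern.** There are two linked problems.

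**The claim about MAR is wrong as written.** Whether data are MAR or MNAR turns on whether missingness still depends on the unseen values once the observed ones are accounted for. A regression on observed baseline data has no information on that. The text therefore tells the reader that an assumption has been replaced by a test, while the estimators it names bring the assumption back.

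**The covariates do not match a known source of missing data.** The withdrawal rule acts on post-baseline BDI-II. The missingness model contains baseline predictors only, and the primary models as described contain no BDI-II. Likelihood or imputation can ignore this dropout only if the scores that caused it are in the model. At stake are a misleading account of what the analysis assumes and an avoidable attenuation of the treatment contrast.

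**Working it through.** **1. The plan's own related figures.** The article states no figure for the missing-data mechanism. The two nearest figures reproduce and are not in dispute.
- Withdrawal example (Treatment Regimen): 22.98 × 1.2 = 27.6, which rounds to the stated 28.
- Sample size with 20% attrition (Power): one-way ANOVA, three groups, medium effect taken as f = 0.25 (assumed), gives 52.4 per group. Then 52 / 0.8 = 65 per group, and 3 × 65 = 195, as stated.

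**2. Can a baseline regression test MAR?** Assumed set-up: standardised baseline and week-8 scores correlated 0.5, with two missingness mechanisms.

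| Mechanism | Missing | Baseline odds ratio | MAR-based week-8 mean | True mean |
|---|---|---|---|---|
| MCAR | 20.0% | 0.996 | 0.005 | 0.004 |
| MNAR (depends on the part of week 8 unrelated to baseline) | 20.7% | 0.996 | −0.172 | 0.004 |

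The regression gives the same answer in both cases. The MAR-based estimate is right in one and off by 0.172 + 0.004 = 0.176 SD in the other.

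**3. What would the baseline model show about rule-driven dropout?** Inputs: BDI-II mean 22.98 and SD 11.58 (Treatment Regimen); correlation between visits assumed.

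| Assumed correlation | Removed before week 8 | AUC, baseline BDI-II | AUC, week-4 BDI-II change | Baseline-only test significant, n = 90 |
|---|---|---|---|---|
| 0.60 | 23.9% | 0.795 | 0.955 | 99.5% |
| 0.75 | 20.5% | 0.767 | 0.955 | 98.2% |
| 0.85 | 16.8% | 0.750 | 0.956 | 88.0% |

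The threshold is a percentage of baseline, so low scorers cross it more easily and the baseline model usually flags them. It credits the dropout to baseline and cannot show that later scores drove it.

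**4. Effect on the week-8 HDRS contrast.** Control versus one active arm, 400,000 simulated participants, with the rule as the only cause of dropout. Assumptions:
- HDRS follows the underlying BDI-II course at half scale, with residual SD 3 and visit-level error correlation 0.5 with BDI-II.
- The active arm declines by 0.3 or 0.8 BDI-II points per week.
- The SD of individual slopes is 0.5 or 1.0 per week.

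The HDRS-only estimate uses HDRS at weeks 0 and 4. The other adds BDI-II at weeks 0, 2, 4 and 6. Shrinkage = (|true| − |HDRS-only|) / |true|.

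| Corr. | Slope SD | Decline | True | HDRS-only | With BDI-II | Shrinkage |
|---|---|---|---|---|---|---|
| 0.60 | 0.5 | 0.3 | −1.20 | −1.18 | −1.21 | 0.02 (1.7%) |
| 0.60 | 0.5 | 0.8 | −3.11 | −3.06 | −3.10 | 0.05 (1.6%) |
| 0.60 | 1.0 | 0.3 | −1.15 | −1.10 | −1.15 | 0.05 (4.3%) |
| 0.60 | 1.0 | 0.8 | −3.10 | −2.99 | −3.11 | 0.11 (3.5%) |
| 0.85 | 0.5 | 0.3 | −1.18 | −1.15 | −1.18 | 0.03 (2.5%) |
| 0.85 | 0.5 | 0.8 | −3.07 | −2.99 | −3.06 | 0.08 (2.6%) |
| 0.85 | 1.0 | 0.3 | −1.16 | −1.08 | −1.16 | 0.08 (6.9%) |
| 0.85 | 1.0 | 0.8 | −3.03 | −2.82 | −3.04 | 0.21 (6.9%) |

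The control-arm week-8 mean is biased by −0.14 to −0.46 points with HDRS alone, and by −0.01 to −0.02 with BDI-II added.

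**5. A separate simulation with other assumptions** (HDRS SD 6, latent loading 0.7, 300,000 per arm), shown as true / HDRS-only / with BDI-II:
- Correlation 0.9, BDI-II change SD 8, BDI-II effect −10: −3.656 / −3.406 / −3.652. Shrinkage is 0.250 / 3.656 = 6.8%.
- Correlation 0.8, change SD 8, effect −5: −1.801 / −1.692 / −1.798. Shrinkage is 0.109 / 1.801 = 6.1%.
- Change SD 4: no material bias.

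**The case against.** The other side can fairly say that the error is one sentence. Imputation or likelihood will be used whatever the test shows, so no stated analysis depends on it, and the article does not say how a null result would be reported. This stands, and it is why the point concerns what is claimed and what is modelled, not a wrong decision rule.

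The bias is also small. With an assumed HDRS SD of 6 and 24 completers per arm (30 × 0.8), the unadjusted standard error of an arm contrast is 6 × √(2/24) = 1.73 points, so 0.25 points is about 0.14 of a standard error. The earliest trigger is weeks 2 and 4 together, and Table 4 schedules HDRS at week 4. Anyone removed before week 8 would therefore normally contribute week-0 and week-4 HDRS, which carries part of the information. This also stands, and the simulation in step 4 already allows for it.

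Several stronger readings are tempting but not supported:
- *The missingness test is blind to rule-driven dropout.* It is not. In step 3 it was significant in 88% to 99.5% of runs. It lacks only the means to attribute the dropout to later scores.
- *The withdrawal rule makes the data MNAR.* It does not. Rule-driven missingness is MAR given the observed BDI-II.
- *The rule is the main cause of dropout.* The article gives no such share. Criteria for Early Discontinuation lists lack of time, interest or motivation first, and the 20% attrition comes from the preliminary study and psychotherapy trials.
- *BDI-II is excluded from the imputation model.* No imputation model is specified, so this cannot be said. The gap is in the models that are described.
- *The lack of an MNAR sensitivity analysis is a defect.* It may be in an analysis plan that is not shown, so it is not counted here.

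**Conclusion.** The point holds in this limited form. The statement that MAR is tested instead of assumed is incorrect on its face and conflicts with the methods named in the same paragraph and under Aim 1. This part rests on logic and needs no numerical assumption. The second part, that the described HDRS, SDS and TMT-4 models do not condition on the variable that triggers withdrawal, is real but modest. The HDRS shrinkage is toward the null, and the simulations on which it rests assume correlations, slope variation and an HDRS–BDI-II relation that the article does not give. The size for SDS and TMT-4 is unknown. The correction is worth making because it costs almost nothing, and because by the article's own Power section the trial has 90 participants against the 195 it calculates for a medium effect. No view is taken on the withdrawal rule itself.

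**What to change.** Replace the sentence on MCAR and MAR with: *The primary analysis assumes MAR; the logistic models check MCAR and describe predictors of dropout and do not test MAR.*

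Include BDI-II at weeks 0, 2, 4 and 6 as auxiliary variables, either in the imputation model or in a joint likelihood with each primary outcome. They should not enter the outcome model as ordinary covariates, because post-baseline scores may carry part of the treatment effect.

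Optionally, if the full analysis plan does not already have one, add a delta-adjusted MNAR sensitivity analysis for the week-8 contrasts.

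The cost is a change of wording and slightly more modelling work. All the BDI-II scores are already scheduled, and neither the sample size nor trial conduct changes.
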